### **3.8.3 Health Economic Endpoints**

Health economic endpoints will be analyzed using descriptive statistics.

### **3.8.4 Exploratory Endpoints**

Exploratory endpoints will be analyzed using descriptive statistics.

### **3.8.5 Subgroup Analyses**

In order to examine the consistency of the treatment effect, the primary analysis will be repeated within predefined subgroups in the FAS. These subgroups will include the randomization strata. For each subgroup, the estimated growth velocity in each treatment group, the estimated difference in growth velocity between treatments and the corresponding 95% confidence intervals will be presented. *P* values will not be presented. The relationship between growth velocity and gestational age at birth will be assessed and presented graphically for each treatment.

Further subgroup analyses may be defined in the statistical analysis plan.

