### 3.6 Study Treatments

#### 3.6.1 Method of Assigning Patients to Treatment Groups

Patients will be randomly assigned to receive either rhBSSL or placebo.

An interactive voice recognition system (IVRS) will be used for the randomization. Biostatistics will generate the randomization schedule for IVRS, which will link sequential patient randomization numbers to treatment codes. The randomization will be stratified by feeding regimen (PBM or infant formula) and by size for gestational age category (SGA or AGA). An infant having a birth weight that lies above the 10th percentile for the gestational age on the gender-specific intrauterine growth curves presented by [Olsen et al 2010](#) is defined as AGA. An infant with a birth weight at or below the 10th percentile is defined as SGA. In this study at least 10% of the infants will be SGA at birth and at least 15% of the infants will be fed with PBM.

The randomization numbers will be blocked, and within each block the same number of patients will be allocated to each treatment group. The block size will not be revealed.

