## **3.6.5 Food Requirements**

### **3.6.5.1 Daily Volume of Enteral Feeding**

Before inclusion of the first patient, each study center must determine a target food volume, to be used for all infants in the study. This volume should be in the range of 150 to 180 mL/kg/day. Once an infant has reached the target volume, the food volume should not be changed during the treatment period. Reasons for departure from the determined target volume must be recorded in the eCRF.

The daily volume (mL) of food enterally fed to the patient will be recorded in the eCRF every day during the treatment period ([Table 6–1](#)). The volume recorded should take into account the food that remained in the bottle at the end of feeding.

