### 3.6.5.3 Infant Formula Requirements

Each study center will select one infant formula that all formula fed patients at that study center will be fed. They will remain on the same infant formula throughout the treatment period, unless medically contraindicated. The exact brand name of the infant formula used should be recorded in the eCRF to enable the composition to be derived.

The range of protein, carbohydrate, and lipid content for the infant formulas allowed for use in this study are

**Protein:** 2.8 to 4.1 g/100 kcal

**Carbohydrate:** 9.5 to 12.0 g/100 kcal

**Lipids:** 4.4 to 6.0 g/100 kcal

In addition, all infant formulas to be used in the study must contain AA and DHA. The infant formula must contain less than or equal to 40% of medium-chain TGs.

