### 3.7.6 Sample Size Calculations

Assuming a true difference in growth velocity between rhBSSL and placebo of 2.25 g/kg/day at 4 weeks and a standard deviation of 7 g/kg/day, 205 evaluable patients in each treatment arm provide 90% power to demonstrate that rhBSSL improves growth velocity compared with placebo (using a 2-sided test with a significance level of 5%). Allowing for 5% of patients to be excluded from the FAS, it is estimated that 432 patients will be randomized. These assumptions are based on the meta-analysis of Sobi's 2 previous Phase 2 studies; the estimate of standard deviation has been increased by 30% to allow for greater variability within the Phase 3 study population.

The sample size calculation was performed using nQuery Advisor software Version 4.0 (Statistical Solutions, Ltd, Cork, Ireland).

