#### 3.8.1 Primary Efficacy Analysis

The null and alternative hypotheses are defined for the primary efficacy variable (growth velocity during the 4 weeks of treatment):

$$H_0: \mu_{\text{rhBSSL}} = \mu_{\text{placebo}}$$

$$H_A: \mu_{\text{rhBSSL}} \neq \mu_{\text{placebo}}$$

In order to calculate growth velocity, the natural log-transformed value of the baseline and all postbaseline weight assessment for each patient will be calculated. A linear regression model will then be fitted for each patient with a response variable of log(weight) and a predictor variable of time. Growth velocity for each patient will be estimated as the slope arising from the regression model, and will need to be multiplied by 1000 for conversion into the desired unit of grams per kilogram per day. The weight over time for each treatment group will be

illustrated graphically and if the log-transformed data clearly deviate from the linearity assumption, a sensitivity analysis will be performed using untransformed data.

Statistical analysis for the primary efficacy variable will be performed using an analysis of covariance model including factors for treatment, feeding regimen (PBM or infant formula), size for gestational age category (SGA or AGA), with baseline weight included as a covariate. For the comparison between treatment groups, the point estimate and the associated 95% confidence interval and *P* value from the model will be presented.

The assumptions of normality and homogeneity of variance will be assessed by inspection of normal probability plots and residual plots. If either assumption is clearly not met, a corresponding nonparametric analysis will be performed (using the same analysis of covariance model, but using ranked response and covariate) to check the robustness of the results.

It is anticipated that the withdrawal rate from the study after randomization will be approximately 15%. For the primary analysis, if patients withdraw before 4 weeks then growth velocity will be derived using weight assessments up to their last available assessment. Sensitivity analyses will be conducted to assess the impact of missing data.

The methods for handling of missing data will be fully described in the SAP.

The primary efficacy variable will be analyzed using both the FAS (the primary population for efficacy evaluation) and PPS (supportive).

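### The primary ANCOVA in section 3.8.1 leaves out gestational age and sex, both available at baseline, so some precision may go unused; the model is valid as it stands

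*Protocol*

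**What the plan says.** Section 3.8.1 lists the terms of the primary model: treatment, feeding regimen, SGA/AGA category, "with baseline weight included as a covariate". It leaves missing-data handling to the SAP, but not this list.

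The omitted variables are to hand. Section 3.4.2.1 has sex, actual birth date and expected birth date recorded at Baseline. The Definitions of Terms say how gestational age is to be determined. Section 3.8.5 then gives gestational age a descriptive role: "The relationship between growth velocity and gestational age at birth will be assessed and presented graphically for each treatment".

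Randomization (section 3.6.1) is stratified by feeding regimen and SGA/AGA only. SGA/AGA is itself defined by comparing birth weight with sex-specific growth curves for gestational age.

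Centre is neither a stratum nor a model term, yet it fixes part of the nutrition. Under section 3.6.5.1, "each study center must determine a target food volume, to be used for all infants in the study", within 150 to 180 mL/kg/day. Under section 3.6.5.3, "Each study center will select one infant formula that all formula fed patients at that study center will be fed".

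**The concern.** The endpoint is weight gain in preterm infants who differ in maturity and sex. Both characteristics are known before the first dose and cannot be affected by treatment. If either predicts growth velocity beyond what the planned covariates capture, leaving it out puts explainable variation into the residual and widens the confidence interval for the treatment effect.

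The same thought arises for centre, because target feed volume and formula differ between centres by design.

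What is at stake is the width of the interval and a modest amount of power. The validity of the comparison is not in question.

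**Working it through.** **Inputs.** From section 3.7.6: "Assuming a true difference in growth velocity between rhBSSL and placebo of 2.25 g/kg/day at 4 weeks and a standard deviation of 7 g/kg/day", a two-sided 5% test, and "205 evaluable patients in each treatment arm provide 90% power". From section 3.6.1, 1:1 allocation: "within each block the same number of patients will be allocated to each treatment group". From section 3.2: about 70 centres. Not in the protocol, and so assumed: the extra share of variance (R²) explained by gestational age and sex beyond the planned terms.

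**Step 1: reproduce the plan's figure.** The standard error of the difference is 7 × √(2/205) = 0.691. The noncentrality is 2.25/0.691 = 3.25. With the noncentral t on 2 × 205 − 2 = 408 degrees of freedom, power is 90.1%, and 205 is the smallest number per arm that reaches 90%. Allowing for 5% exclusions, 410/0.95 = 431.6, which rounds up to 432. The plan's figures are correct.

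**Step 2: degrees of freedom.** The planned model leaves 410 − 5 = 405 residual degrees of freedom (intercept plus four terms). Adding gestational age and sex leaves 403. Using 403 instead of 408 changes the power figures by less than 0.01 percentage points.

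**Step 3: effect of the two covariates.** Residual SD = 7 × √(1 − R²), with 205 per arm. The 95% half-width is 1.96 × SE.

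| Assumed extra R² | Residual SD | SE | 95% half-width (g/kg/day) | Power |
|---|---|---|---|---|
| 0 | 7.00 | 0.691 | 1.36 | 90.1% |
| 0.02 | 6.93 | 0.684 | 1.34 | 90.7% |
| 0.05 | 6.82 | 0.674 | 1.32 | 91.5% |
| 0.10 | 6.64 | 0.656 | 1.29 | 92.8% |

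This treats 7 g/kg/day as the residual SD under the planned model. If the planned covariates already bring it below 7, starting power is above 90.1% and there is less left to gain.

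**Step 4: centre.** With 410/70 ≈ 5.9 infants per centre and randomization not stratified by centre, many centres will be unbalanced between arms. In simulation, fitting 70 fixed centre effects multiplies the variance of the treatment estimate by about 1.20 (centres of equal expected size) or 1.17 (unequal).

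- Break-even centre share of variance: 1 − 1/1.202 = 0.168, or 1 − 1/1.168 = 0.144.
- Power with fixed effects if centre explains nothing: about 84% to 85%.
- Power with fixed effects if centre explains 10%: about 88% to 89%.

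A random intercept avoids this cost. With the variance components taken as known, it leaves power at about 90% when centre explains nothing. At a 10% centre share it cuts the variance by only about 4% to 5%, for a power a little over 91%. It recovers part of the centre variance, not all of it.

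**The case against.** The strongest reply is that this is a preference. A short pre-specified covariate list that contains both strata is sound practice, the trial has its stated power without any covariate credit, and the suggestion that another covariate might help can be made of almost any ANCOVA. The extra R² may also be close to zero. Baseline weight is in the model, SGA/AGA is built from sex and gestational age, and eligibility restricts maturity (birth before Week 32, under 33 weeks postmenstrual age at randomization). All of this stands. It limits the size of the point and is why the range above starts at zero. It does not remove the point, because two baseline terms cost almost nothing.

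Four stronger readings are tempting, and the protocol does not support them.

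- A reader might take the gestational-age graph in section 3.8.5 as an admission that growth velocity depends on gestational age. It sits among analyses of the consistency of the treatment effect. Planning to look at a relationship does not presume that one exists, and that section does not state the model.
- A reader might conclude that precision is definitely lost. The protocol reports no association of gestational age, sex or centre with growth velocity.
- A reader might see chance imbalance across centres as distorting the treatment comparison. It is random error, already reflected in the standard error, and not bias.
- A reader might convert the gain into fewer infants. Section 3.8.7 rules out any decrease in sample size, so none would be saved.

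**Conclusion.** The point holds as an optional improvement. The primary model is valid and unbiased and delivers the stated 90% power; no figure in the protocol is wrong. Leaving out gestational age and sex may forgo some precision: nothing at an extra R² of 0, about 0.6 power points at 0.02, 1.4 at 0.05 and 2.7 at 0.10. Over that range the 95% half-width narrows from 1.36 to at most 1.29 g/kg/day.

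These sizes rest on assumed R² values and on 7 g/kg/day as the starting residual SD. The overlap with baseline weight and SGA/AGA suggests the lower part of the range is at least as plausible as the upper.

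The case for centre is weaker. Centre-set feed volume and formula make a centre effect plausible, but the protocol gives no size for it. Fixed centre terms would reduce power unless centre explained more than about 14% to 17% of the variance.

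**What to change.** Before unblinding, add two covariates to the model in section 3.8.1: gestational age at birth (or postmenstrual age at baseline) and sex. Name one of the two age measures in advance, and keep the current four-term model as a sensitivity analysis. Because section 3.8.2 models several secondary endpoints on the primary approach, state there whether the added terms carry over.

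If centre is to be examined, add a sensitivity analysis with a random intercept for centre. Do not fit about 70 fixed effects.

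The cost is a sentence or two of text and 2 of 405 residual degrees of freedom. No new data are needed, and the sample size does not change.

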### **3.8.6 Safety Analyses**

Safety analysis will be performed for vital sign measurements, laboratory safety results, tolerability, withheld enteral feeding during 24 hours, ECG findings, vitamin A and D levels, antibodies against rhBSSL, Bayley-III (composite scores for the cognitive, language and motor domains at 12 months corrected age), and AE data collected up to 3 months and SAE data up to 12 months corrected age.

A separate safety analysis will be performed for serious ADRs collected up to 24 months corrected age.

### **3.8.6.1 Adverse Events**

All AEs will be coded using the latest version of MedDRA. All treatment-emergent AEs will be summarized showing the number of patients who experienced an event, the percentage of patients with that event, and the severity, duration, and relationship to study drug. Percentages will be based on the number of patients who received each treatment during the study.

The incidence of SAEs, including death, serious ADRs and AEs leading to study drug discontinuation will also be tabulated.

### **3.8.6.2 Clinical Laboratory Results**

Clinical laboratory safety test data will be presented using summary statistics. Laboratory normal ranges are not available for preterm infants. Values will be assessed for clinical significance by the investigator and all clinically significant abnormal results will be entered as AEs in the source documents and the eCRF. The number and proportion of patients experiencing clinically significant events during the treatment period will be presented.

### **3.8.7 Interim Analyses**

In order to establish whether the assumptions used to calculate the sample size are appropriate, an blinded interim analysis (IA) will be conducted once 200 patients have been randomized and followed up to 4 weeks or discontinuation (whichever occurs first). At the IA, growth velocity will be calculated for each patient. The overall standard deviation of the growth velocity data will be calculated, and the within-group standard deviation will be estimated using the assumption that the treatment effect is an increase in mean growth velocity of 2.25 g/kg/day as anticipated in the sample size calculations. The sample size calculation will be re-performed using the estimated within-group standard deviation, with all other assumptions remaining unchanged. Sobi will use the IA results to decide whether the sample size of the study should be increased in order to ensure the primary objective can be reliably assessed. The sample size will be increased up to a maximum of 534 evaluable patients, which corresponds to 564 randomized patients assuming a withdrawal rate of 5% from the FAS. The proposed maximum corresponds to a standard deviation of 8.0 g/kg/day. Regardless of the IA result, the sample size will not be decreased, or increased beyond the proposed maximum. As this is a blinded analysis, there is no impact on the overall power or

Type I error rate. Data contributing to the IA will be fully cleaned, and a full analysis plan for the IA will be written before the analysis is conducted.

The DSMB will review selected safety data on an ongoing basis ([Section 5.4](#)).

### **3.8.8 Analysis of Data Up to 12 Months**

All available data up to the 12-months-corrected-age visit will be analyzed when all patients have completed the 3-month visit and 200 patients have completed the 12-months-corrected-age visit, including the Bayley assessment. The results will be reported in a clinical study report. When all patients have completed their 12-month visit, complementary analyses of 12-month data (ie, after the 3-month visit and up to the 12-month visit) will be performed and reported in an addendum to the clinical study report.

### **3.8.9 Analysis of 24-months Data**

The analysis of the 24-months-corrected-age assessments, as well as the health economic assessments and any serious ADRs will be performed when the last patient has completed the 24-months-corrected-age visit. The results of this analysis will be reported in a separate clinical study report.

### **3.8.10 Combining Data**

A prospective protocol with the purpose of combining data from this study with data from other possible future studies will, if applicable, be written.

## **3.9 Data Quality Assurance**

During study conduct, PPD will conduct periodic monitoring visits to ensure that the protocol and Good Clinical Practice are being followed. The monitors will review source documents to confirm that the data recorded in eCRFs are accurate. The investigators and institutions will allow PPD monitors and appropriate regulatory authorities access to source documents to perform this verification.

The study center may be subject to review by the independent ethics committee (IEC) and to quality assurance audits performed by Sobi, or companies working with or on behalf of Sobi, and to inspection by appropriate regulatory authorities.

Investigators and their relevant personnel must be available during the monitoring visits and possible audits or inspections and sufficient time must be devoted to the process.

## **4 Investigator's Obligations**

The following administrative items are meant to guide the principal investigator or subinvestigator in the conduct of the study but may be subject to change based on industry and government standard operating procedures, working practice documents, or guidelines. Changes will be reported to the IEC but will not result in protocol amendments.

### **4.1 Confidentiality**

All laboratory specimens, evaluation forms, reports, and other records will be identified in a manner designed to maintain patient confidentiality. All records will be kept in a secure storage area with limited access. Clinical information will not be released without the written permission of the patient's legally acceptable representative, except as necessary for monitoring and auditing by the sponsor, the sponsor's designee, the regulatory authorities, or the IEC.

The principal investigator or subinvestigator and all employees and coworkers involved with this study may not disclose or use for any purpose other than performance of the study, any data, record, or other unpublished, confidential information disclosed to those individuals for the purpose of the study. Prior written agreement from the sponsor or its designee must be obtained for the disclosure of any said confidential information to other parties.

### **4.2 Institutional Review**

Regulations and the ICH guidelines require that approval be obtained from an IEC before participation of human patients in research studies. Before study onset, the protocol, ICF, advertisements to be used for the recruitment of study patients, and any other written information regarding this study to be provided to the patient's legally acceptable representative must be approved by the IEC. Documentation of all IEC approvals and of the

IEC compliance with ICH harmonised tripartite guideline E6(R1): Good Clinical Practice will be maintained by the study center and will be available for review by the sponsor or its designee.

All IEC approvals will be signed by the IEC chairman or designee and must identify the IEC name and address, the clinical protocol by title or protocol number or both, and the date approval or a favorable opinion was granted.

The principal investigator or subinvestigator is responsible for obtaining continued review of the clinical research at intervals not exceeding 1 year or otherwise specified by the IEC. The principal investigator or subinvestigator must supply the sponsor or its designee with written documentation of continued review of the clinical research.

### **4.3 Informed Consent**

Before being admitted to the clinical study, the patient's legally acceptable representative must have expressed his or her consent to participate, after clear explanations about the nature, scope, and possible consequences of the clinical study have been given to them by the investigator or designee.

Informed consent will also be collected from the patient's legally acceptable representative for the 24-months-corrected-age assessments, as well as the health economic assessments and any serious ADRs. This consent will be collected when amendment 2 has been implemented and earliest at the 12-months-corrected-age visit. In addition, informed consent will be collected from the legally acceptable representatives for the collection of confounders of neurodevelopment.

If consent to continue into the extension study is refused then data will be collected as per the original protocol, up to and including the 12-months-corrected-age visit. The patient will follow the end of study procedures as described in the original protocol and no further data will be collected.

Information will be given in both oral and written form. The informed consent information sheets will include all the elements required by law following the ICH E6(R1) guidelines. The informed consents will be approved by the IEC (and regulatory authorities) of each study center.

In addition to the standard requirements that physicians are currently obliged to observe when providing information, the following points must also be covered:

- A description of the objectives of the study and how it will be organized
- The type of treatment
- Any potential negative effects attributable to the study drug
- The freedom to ask for further information at any time
- The patient's legally acceptable representative's right to withdraw the patient from the clinical study at any time without giving reasons and without jeopardizing the patient's further course of medical treatment
- The existence of patient insurance coverage and a summary of what is included in this coverage

Adequate time and opportunity to satisfy questions will be given to the patient's legally acceptable representative.

The investigator will be supplied with an adequate number of ICFs to be used. The forms will be signed and dated by both the investigator or designee and the patient's legally acceptable representative before the beginning of the study. A copy of the signed forms will be given to the patient's legally acceptable representative.

To ensure medical confidentiality and data protection, the signed ICFs will be stored in the investigator's study file. The investigator will allow inspection of the forms by authorized representatives of the sponsor, IEC members, and regulatory authorities. The investigator will confirm, by signing and dating the eCRFs, that informed consent has been obtained.

